# Abbreviations

| EGFR  TK | Epidermal Growth Factor Receptor  Tyrosine kinase |
| --- | --- |
| TKD  TKI  NSCLC | Tyrosine kinase domain  Tyrosine kinase inhibitor  Non small cell lung cancer |
| ALT | Alanine aminotransferase |
| AP | Alkaline phosphatase |
| AST | Aspartate aminotransferase |
| CR | Complete response |
| GGT | Gamma-glutamyltransferase |
| HIV | Human immunodeficiency virus |
| IV | Intravenous |
| LDH | Lactate dehydrogenase |
| NA | Not available |
| NE | Not evaluable |
| OR | Objective response according to RECIST criteria |
| PD  CR | Progressive disease  Complete response |
| PR | Partial response |
| SD | Stable disease |
| TTP | Time to progression |
| OS | Overall survival |

# Protocol synopsis

| **Title**  PROSPECTIVE EVALUATION OF SMALL MOLECULE EGFR-1 TYROSINE KINASE INHIBITION AS A FIRST-LINE TREATMENT IN PATIENTS WITH ADVANCED NON-SMALL CELL LUNG CANCER (NSCLC) HARBOURING A MUTANT EGFR GENE |
| --- |
| **Sponsor / Study Coordination**  Dienst Medische Oncologie - Oncologisch Centrum  Academisch Ziekenhuis Vrije Universiteit Brussel |
| **Study hypothesis**  Erlotinib is a safe and effective first-line treatment for NSCLC harboring a mutant EGFR |
| **Study design**  One arm, multicenter investigator initiated phase II study. |
| **Primary objective**  To investigate the efficacy and feasibility of using a small molecule EGFR inhibition in the first-line treatment of non-small cell lung cancer carrying (a) EGFR kinase domain mutation(s) not amenable to curative treatment. |
| **Primary endpoint**  Progression free survival time. |
| **Secondary objectives**  Objective response rate according to the RECIST criteria, metabolic response rate Feasibility, toxicity, duration of response and survival (TTP and OS from the date of study entry). |
| **Secondary endpoints**   - Toxicity according to the NCI-CTCAEv3 criteria. - Feasibility (reported descriptively). - Duration of response - Overall survival (from the initiation till PD). |
| **Patient selection criteria**   - - **Identification of an EGFR TKD mutation in the tumor material of the patient.** - No previous chemotherapy for metastatic disease. - Patients in whom any other anticancer treatment is needed after inclusion in the study will be considered to have met the primary endpoint. - Standard phase II recruitment criteria. |

| **Treatment plan and special procedures**  Patients will remain in the study under continuous treatment with erlotinib as long as they remain progression free, receive no other secondary anticancer treatment and remain free from unacceptable toxicity. |
| --- |
| **Study treatment duration, discontinuation and study withdrawal**   - At any time during study, progression of disease, unacceptable toxicity or patient refusal will result in study treatment discontinuation. - Patients that stop study treatment for other reasons than progressive disease must be followed by serial assessment of their response status as provided by the protocol |
| **Statistical considerations**  **Design**: phase II  **Nr of patients**: based on results obtained with chemotherapy a progression free survival of >= 60% could be expected at 3 months. The treatment will be considered for further development if a PFS > 70% can be obtained at 3 months. The treatment will be considered inappropriate as a first line if PFS < 50% at 3 months. Therefore a maximum of 40 patients will be included plus the number needed to replace patients that will drop out for reasons other than disease progression and patients not meeting eligibility criteria. |

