# Study design and conduct.

Patients diagnosed with advanced non-small cell lung cancer and meeting the selection criteria can be considered for study inclusion. Patients concomitantly receive the Informed Consent form for mutation analysis of their tumor material and the Informed Consent for the treatment phase of the study. The Informed Consent for the mutation analysis includes the possibility for a repeat biopsy if the available material is insufficient and a biopsy is possible and safe. It also includes the possibility of performing a second biopsy (if possible and safe) upon progression under protocol treatment for study of secondary resistance mechanism. After obtaining both consents, the baseline examinations needed for the study can be performed in parallel to the mutation analysis, the result of which should be available within 2 weeks. Patients will be included in the study after filing of the inclusion form with the central data management and principle investigator. Eligibility for subsequent protocol treatment depends on the identification of a kinase domain mutation in the TK domain of the EGFR.

The maximal interval allowed between baseline exams and initiation of study is 3 weeks.

After documentation of unequivocal objective progression the patients will go off study. If the patient leaves the study because of unacceptable toxicity or any other reason without progressive disease, the assessments for determination of response duration will continue until disease progression is documented.

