### Time to Progression

The Time to Progression is defined as the time from start of treatment to the date of the first documented progression (according to RECIST criteria) or the date of death for any reason in the absence of PD. Patients who have not died or progressed at the time of the final analysis will be censored at the date of last contact.

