# Statistical considerations

The purpose of this study is to obtain an estimate of the proportion of patients experiencing a progression free survival (PFS) at three months in order to position this type of first-line therapy for further study in comparison to the results that can be obtained with current first-line chemotherapy in advanced non-small cell lung cancer.

The premises for the sample size determination are as follows:

With current chemotherapy, progression free survival of 60% or less is obtained at 3 months follow-up3.

Taking into account the general better tolerability of RTKI’s it is proposed that if a PFS of > 70% can be obtained, that this treatment definitely deserves further evaluation against chemotherapy in the first-line treatment of advanced non-small cell lung cancer.

If the study results in a PFS less than 50 % at three months, single agent RTKI’s should not be further evaluated in this setting as outcomes inferior in terms of efficacy to the current standard are not acceptable.

Based on these premises, a one step Fleming design requires at least 33 patients to be included in the study (

With the provision of a margin for eligibility/evaluation issues, the prospective number of patients to be included will be 40 patients.

When, alternatively, statistics normally used for phase II design based on response, are applied to the PFS outcome proportions (freedom from progression regarded as a clinical benefit response), then, in a Simon minimax two-stage design and with α = 5%, β = 20%, for rejecting the null hypothesis (p0) of a freedom from progression rate < 60%, in a first stage, more than 8/13 patients should have a progression free survival of > 3 months. The second stage would lead to an accrual of 35 evaluable patients of whom at least 26 should be free from progression at 3 months to establish a probable freedom from progression rate of > 80% at 3 months. Again, with the provision of a margin for eligibility/evaluation issues, the prospective number of patients to be included will be 40 patients.

With an estimated maximal 10% mutation rate in the overall population of NSCLC, this cohort of patients could result from a baseline population of at least 400 patients with advanced non-small cell lung cancer.

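### The synopsis rule that replaces non-progression drop-outs conflicts with the protocol's own event and follow-up rules, and can take treated patients out of the 3-month PFS denominator

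*Protocol*

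**What the plan says.** **Replacement.** Under the number of patients, the synopsis states "Therefore a maximum of 40 patients will be included" and continues "plus the number needed to replace patients that will drop out for reasons other than disease progression and patients not meeting eligibility criteria". It does not define drop-out.

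**Sample size.** Section 15 (Statistical considerations) has no drop-out replacement. There the 40 already contains the allowance: "With the provision of a margin for eligibility/evaluation issues, the prospective number of patients to be included will be 40 patients". Its Simon alternative is set "in a Simon minimax two-stage design and with α = 5%, β = 20"%; the null rate is 60%. It requires more than 8 of 13 at stage one, then at least 26 of 35 evaluable patients free from progression at 3 months, with 80% as the target rate. Evaluable is not defined.

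**How the same patients are treated elsewhere.**
- Need for other treatment (synopsis, patient selection criteria): "Patients in whom any other anticancer treatment is needed after inclusion in the study will be considered to have met the primary endpoint".
- Death without progression (section 9.4, Time to Progression): the event date is progression "or the date of death for any reason in the absence of PD".
- Leaving for toxicity or any other reason without progression (section 8): "the assessments for determination of response duration will continue until disease progression is documented". The synopsis and section 9.5 say the same in substance.

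**The only explained use of replacement.** Section 16.1 (Mutation analysis) says that patients whose mutation is not confirmed by sequencing are left out of the final efficacy analysis and are replaced for that reason.

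**The concern.** Replacing an ineligible patient, or one whose mutation is not confirmed, depends on facts fixed before the first dose and does no harm to the estimate. Replacing a drop-out depends on what happened under treatment. Read literally, drop-out for reasons other than progression could cover toxicity, refusal, death without progression and a change of therapy. Other sections make some of these patients events and keep the rest under assessment.

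In a single-arm trial with one go/no-go proportion, the denominator is the analysis. If replaced patients are not counted, and they would have failed more often than the rest, the 3-month rate is too high and an inactive treatment passes too easily. The choice could also be made once the patient's outcome is known. The primary objective in the synopsis covers feasibility as well as efficacy, and section 15 supports the 70% mark by better tolerability. Patients who could not stay on treatment are therefore informative.

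**Working it through.** **Step 1. Reproduce the plan's figure.** With true rate q, the chance of a go under the section 15 rule is

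P(go | q) = Σ (x = 9 to 13) P[Bin(13, q) = x] × P[Bin(22, q) ≥ 26 − x].

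At q = 0.60 this is 0.0499 and at q = 0.80 it is 0.808. An exact search for the minimax design (60% against 80%, one-sided 5%, 80% power) returns the same 8/13 and 25/35 boundaries. The stated design is correct.

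**Step 2. Does the text allow removal?**
- The synopsis says only that such patients are replaced.
- Section 16.1 is the only place where replacement is explained, and there it means leaving the efficacy analysis.
- Section 15 counts evaluable patients without saying who they are.
- Section 12.6 takes patients with a long toxicity-related interruption off study, which fits an ordinary sense of drop-out.

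Removal is therefore a permitted reading, not a stated rule.

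**Step 3. Effect if they are removed.** Let p be the true 3-month rate in all treated patients, d the share replaced, and f the share of those replaced who would have failed by 3 months. The successes left are p − d(1 − f), out of 1 − d, so the apparent rate is

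q = [p − d(1 − f)] / (1 − d).

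There is no bias when f = 1 − p. At p = 0.60 this means f = 0.40. The bias is upward above that and downward below it.

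The protocol gives neither d nor f, so both are assumptions. With p = 0.60 and d = 10%:

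| f | Apparent rate q | P(go) at the null |
|---|---|---|
| 0.20 | 0.52/0.90 = 57.8% | 0.028 |
| 0.40 | 0.54/0.90 = 60.0% | 0.050 |
| 0.50 | 0.55/0.90 = 61.1% | 0.065 |
| 0.75 | 0.575/0.90 = 63.9% | 0.117 |
| 1.00 | 0.60/0.90 = 66.7% | 0.196 |

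Varying d:

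| d | P(go), f = 0.50 | P(go), f = 0.75 | P(go), f = 1 (upper bound) | q at f = 1 |
|---|---|---|---|---|
| 5% | 0.057 | 0.076 | 0.101 | 63.2% |
| 10% | 0.065 | 0.117 | 0.196 | 66.7% |
| 15% | 0.075 | 0.180 | 0.354 | 70.6% |

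**Step 4. What f could be.** For a death or a start of other anticancer therapy before 3 months, f = 1 by the protocol's own definitions. A toxicity or refusal stop is not a PFS event, so its f is unknown. Section 7.3 leaves treatment to the investigator's discretion once protocol treatment has permanently ended, so some of these patients could become events through a change of therapy. Performance status 0 to 3 is admitted, so early deaths without documented progression are plausible.

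**Step 5. In counts.** 26/35 = 74.3% just meets the rule. If three replaced failures are restored, it becomes 26/38 = 68.4%, below the 70% mark. With five it is 26/40 = 65.0%.

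**The case against.** The strongest reply is that the synopsis sentence concerns recruitment numbers and not the analysis set. Where the protocol wants exclusion it says so, as in section 16.1, and it has no such clause for drop-outs. A coherent reading exists in which drop-out means lost before the 3-month status is known, and the analysis set may be defined in an SAP that is not shown. This stands to the extent that removal is an inference. It does not dispose of the point, because the replacement rule itself is in the protocol, operates during accrual, and conflicts with other sections of the same document.

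A reader might infer that the protocol does remove toxicity stops, deaths and switches, and so does inflate PFS. The documents do not support that. Deaths and switches are defined as events. Toxicity stops are followed and count as successes if progression-free at 3 months without other treatment. Losing such successes would lower the rate.

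A reader might also infer that the trial's 5% error is broken. The 5% in the available text belongs to the Simon design, which section 15 offers as an alternative. The synopsis cut-offs of 70% and 50% carry no stated error rate, and the Fleming parameters are cut off in the text available.

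Finally, counting every missing 3-month assessment as a failure is one conservative choice. It departs from the planned Kaplan-Meier analysis, which censors at last contact, and it biases downward. It should not be a required correction.

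**Conclusion.** The concern holds as a conflict with a possible bias. The synopsis replacement rule cannot be reconciled as worded with the event definitions in the synopsis and section 9.4, with the follow-up rules in the synopsis and sections 8 and 9.5, or with section 15, where 40 already includes the margin. Together with section 16.1 and the undefined evaluable patients, it lets treated patients leave the primary denominator because of a post-treatment outcome.

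The size is conditional. At a true rate of 60% with 10% replaced, the Simon rule's false-go risk runs from 0.050 (40% of replaced patients would have failed) to 0.196 (all would have failed), and lies below 0.05 under 40%. The calculation assumes that replaced patients are dropped, that replacements come from the same population and are subject to the same rule, and that 35 patients are counted. The share replaced and their failure rate are assumptions, so the direction of bias is not established. The text needs correcting because the go/no-go result can depend on which section is followed.

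**What to change.** Make these changes in the synopsis and section 15:

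- Limit replacement to patients never treated, found ineligible, or without a confirmed mutation. Delete replacement for other drop-outs, and state once whether 40 includes the margin.
- Keep every other treated patient in the primary analysis, and define evaluable accordingly.
- Count deaths and starts of other anticancer therapy before 3 months as events, as the protocol already does. Follow toxicity and refusal stops to progression and classify them by their actual status.
- Handle patients with no 3-month assessment through the planned Kaplan-Meier estimate, with a sensitivity analysis counting them as failures.
- If more than 35 patients are analysed, restate the decision count. For illustration, a one-stage rule of at least 30 of 40 has type I error 0.035 at 60% and power 0.839 at 80%.

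The cost is wording, and a reported rate that may be slightly less favourable. If exactly 35 such patients are counted under the stated rule, its type I error of 0.0499 and power of 0.808 are kept.

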# Introduction

Patients with stage IV NSCLC and some patients with advanced locoregional disease (stage III) are in general incurable and have a low probability for long-term survival.

Current systemic treatment in good PS patients (PS 0-1) consists of a cisplatin doublet (e.g. cisplatin plus a second drug: vinorelbine, gemcitabine, paclitaxel, docetaxel). The median and one year survival obtained with this treatment ranges between 8-10 months and 25 - 35 % respectively (1,2). Progression-free survival is a median of 5 month or less in randomized studies (3). Response rates obtained are less than 25% in metastatic disease and up to 75% in advanced locoregional disease.

Receptor tyrosine kinase inhibitors (RTKI's) are active drugs in patients with NSCLC pre-treated with cisplatin and/or docetaxel containing chemotherapy (2,4). Recently it has been shown that the EGFR1 kinase inhibitor erlotinib added to best supportive care (BSC) prolonged survival compared to BSC alone in patients with advanced NSCLC failing 1st or 2nd line chemotherapy (5).

A small number of preliminary reports have indicated that the objective response rate with these RTKI's as first line treatment in some patient populations with advanced NSCLC could be around 20 % (6), The objective (mainly partial) response in the phase II studies with pre-treated patients ranges from 10 - 15 % according to the level of pre-treatment but the control of the disease (stable disease) and improvement of symptoms without demonstrated objective response has been reported to be as high as 40 to 50 % (2,4). The addition of RTKI's or placebo to the current standard doublets (e.g. cisplatin, gemcitabine or taxol/carboplatin) has not been shown to impact on response rate, time to treatment failure or survival in large phase III randomised trials in advanced NSCLC patients not selected for EGFR expression (7,8).

Recently, mutations in the intracellular EGFR kinase domain that increase sensitivity of the receptor to RTKI's have been discovered (9,10). These studies suggest that the response/resistance to treatment could be strongly correlated to the presence/absence of such mutations. It is presently unclear whether patients who achieve stable disease under RTKI treatment do have receptor mutations, of which nature such mutations could be or what other biological pathways modulate the responsiveness/resistance.

Mutations have been observed in about 10 % or less of the tumours examined.

Most mutations in the EGFR kinase domain have been found in adenocarcinoma of non-smokers or minimal smokers.

Recent data have established that an EGFR mutation can be found in 30% of adenocarcinoma of the lung if the smoking history is maximally 15 years. The probability of finding a mutation is approximately 50% in never-smokers with adenocarcinoma (11).

In contrast to the rather low objective response rate, the clinical benefit rate of treatment with RTKI is around 40 % in a general population of non-small lung cancer (9,10), more than can be accounted for by mutational analysis. EGFR gene amplification might be another determinant for sensitivity, but the biological factors leading to disease stabilisation in some patients with non-activated EGFR are presently unknown.

Several humanized monoclonal antibodies (huMoAb) that can inhibit the EGFR-1 receptor have been developed as well. Of these, cetuximab (Erbitux) has been developed most extensively, especially in head and neck (12) and colorectal cancer (13,14), but other, fully humanized antibodies (huMoAb) (ABX-EGF, EMD 72000) are under development.

Cetuximab has been assessed in NSCLC, especially in combination with first-line and second-line chemotherapy (15), but no data are currently available with respect to single agent activity.

The two types of currently available drugs targeting the EGFR-1, the RTKI's such as gefitinib and erlotinib and huMoAb such as cetuximab and ABX-EGF, are generally well tolerated and devoid of significant grade 3-4 toxicity.

While there are strong indications that the major responses obtained with RTKI’s could strongly correlate with the presence of tyrosine kinase domain mutations in addition to the known mechanism of action of these drugs (16,17), this is at present yet not so clear for the monoclonal antibodies directed against the extracellular domain of the receptor.

Some recent data suggest that EGFR gene amplification might also correlate with response to TKI (18).

Patients with Stage IV and some advanced stage III NSCLC are at present incurable and first-line chemotherapy has had only a palliative and a life prolonging effect at a cost of variable toxicity.

On the other hand the response rate to TKI in patients with a NSCLC carrying a mutant receptor is probably high as can be inferred from the comparison of the prevalence of such mutations and the response rate to these agents in an unselected population (16).

It seems therefore reasonable to explore in a first-line setting the potential of EGFR-1 targeted therapy, as these drugs have a very favourable toxicity profile and might induce prolonged palliation.

There are currently no data that would suggest that delaying chemotherapy in this patient population in well controlled conditions and for a limited time period (sufficient to evaluate the efficacy of more novel first-line treatments) might affect the efficacy of subsequent chemotherapy. There are also no data that suggest that prior administration of drugs targeted at the EGFR-1 will induce resistance to subsequent chemotherapy. The distinct respective mechanisms of action of these drugs and chemotherapy also do not suggest this to be likely.

In other diseases such as prostate cancer and oestrogen receptor-positive breast cancer, the availability of hormonal treatments permits prolonged and at times long-term disease control with limited discomfort. It is possible that a similar scenario could be obtained with an anti-EGFR treatment in NSCLC carrying a mutant EGFR.

Therefore it seems justified to expand previous second-line phase II experience with anti-EGFR strategies to patients with incurable stage III-IV NSCLC without prior therapy and a mutant EGFR. The informed consent towards these patients before entry in the study will clearly state that until now the first-line standard of care has been chemotherapy, which leads to a small overall survival benefit compared to the supportive treatment only and that participation in the current study will delay this treatment within a tightly controlled setting.

In the current trial the RTKI erlotinib will be used. Prior experience with this drug has been obtained in phase II and III studies. In the phase II setting, in an unselected pretreated population, a response rate of 12.3% and a median survival of 8.4 months could be obtained (19). In phase III, placebo-controlled studies, combination of erlotinib with concurrent chemotherapy does not provide a survival advantage (gemcitabine and cisplatin in TALENT (20) and paclitaxel and carboplatin in TRIBUTE (21). Several hypotheses can explain these results: lack of selection of patients; antagonism between cytostatic and cytotoxic agents (negative interaction with chemotherapy when given concurrently); chemotherapy and EGFR inhibitors target the same cell population since chemotherapy directly or indirectly affects EGFR function/expression and thereby reducing the effects of EGFR inhibitors. These results are in contrast to the significant survival benefit seen in the phase III randomized placebo-controlled study in NSCLC following failure of 1st or 2nd line chemotherapy (BR21). The response rate was 9% in the erlotinib treated patients, with significant increase in progression free survival (from 8 to 9,7 wks) and increased survival (from 4.7 mth to 6.7 mth, p< 0.001). In that study the biological parameters that correlate with response (mutation status, EGFR gene amplification and EGFR immunohistochemistry) are still under study.

Survival benefit correlated best with the presence of EGFR expression by immunohistochemistry and EGFR gene polysomy (22).

